### Health economic evaluation

The health economic evaluation will be performed according to the Consolidated Health Economic Evaluation Reporting Standards 2022 Statement [57] and will include the following analyses: (1) a cost-effectiveness analysis using cost per improved case (based on the RCI/CSC) as the outcome, and (2) a series of cost-utility analyses using cost per quality adjusted life years (QALYs) gained for children (using SDQ scores mapped onto a multi-attribute utility instrument using available algorithms), for parents (using the scores from the AQOL-8D) and for the dyad as the outcome.

Costs will be analyzed from two different perspectives: a health care provider perspective and a societal perspective. The health care provider perspective includes the cost to run the intervention (e.g., therapist salary costs, administration) which will be collected from project documentation at the clinic. The societal perspective includes, in addition to intervention costs, other health care costs (health care utilization and medication), as well as costs beyond health care, including social support, and indirect costs related to lost productivity for parents (related to absence from paid and unpaid work) collected via the TIC-P.

Total costs and total QALYs will be aggregated over the trial period and estimated using the area under the curve method [58]. Differences in improved cases, total QALYs and total costs for children and parents before and after the intervention will be analyzed using regression models.

In the cost-effectiveness and cost-utility analyses, we will estimate an incremental cost-effectiveness ratio (ICER) as the ratio between the difference in costs and the difference in improved cases and QALYs for children, parents and the dyad between pre and post intervention for each costing perspective. Uncertainty around the cost and effect data will be explored using non-parametric bootstrapping and plotted on a cost effectiveness plane [59]. The probability of cost-effectiveness of the intervention at different values of willingness to pay will be estimated and represented visually as a cost-effectiveness acceptability curve [60].

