### Participants

The target population is children aged 2–6 years with subclinical levels of NDDs and behavioral problems and their parents. The children have been referred to child health psychologists at the child pediatric outpatient clinic in Uppsala Region and offered the parenting group intervention Everyday Life and Parenting. To be eligible for the project, the parents must attend the intervention and be able to fill in questionnaires and answer weekly measurements in Swedish. Children aged 4–6 years whose parents consent to participate in the project will be invited to participate. No other inclusion or exclusion criteria will be applied.

According to the SCED standard, at least three, preferably five, participants should be included in each baseline condition [32]. The goal in our study is to retain 15 parents and 15 children as participants, i.e., 5 parents and 5 children in each of the three baseline conditions. To take into account an expected drop-out of about 10–20% we will need to recruit about 18 parents and 18 children [33]. This is deemed to be more than sufficient to be able to make detailed SCED analyses.

In terms of pre-, post- and follow-up assessment, we want to be able to detect relatively small effect sizes. To be able to detect an effect size of 0.35 with an alpha of 0.05 and power of 80%, we will need at least 54 participating parents. If we assume a 20% attrition rate, 70 participants will need to be recruited. These results can be compared to randomized studies on similar populations.

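### The only uncertainty method named for the economic evaluation, a bootstrap of trial data, does not carry SDQ mapping error, so child and dyad uncertainty is understated unless this is added.

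*Protocol article*

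**What the plan says.** The Health economic evaluation section of the Protocol article plans cost-utility analyses for children, for parents and for the dyad, each from two costing perspectives. Child utilities are to be obtained "using SDQ scores mapped onto a multi-attribute utility instrument using available algorithms". The same sentence goes on "for parents (using the scores from the AQOL-8D) and for the dyad as the outcome", so parent utilities come from the instrument's own scores and need no mapping.

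QALYs are built up over time: "Total costs and total QALYs will be aggregated over the trial period and estimated using the area under the curve method". The ICER is a contrast "between pre and post intervention for each costing perspective".

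On uncertainty the section says: "Uncertainty around the cost and effect data will be explored using non-parametric bootstrapping and plotted on a cost effectiveness plane". An acceptability curve follows: "The probability of cost-effectiveness of the intervention at different values of willingness to pay will be estimated". It names no other uncertainty method. It does not name the algorithm or the target instrument, and it does not say whether mapping error is carried into the bootstrap. It commits to a reporting standard ("will be performed according to the Consolidated Health Economic Evaluation Reporting Standards 2022 Statement").

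**The concern.** A mapped utility is a prediction. Its coefficients were estimated in another sample and have their own standard errors. A non-parametric bootstrap resamples the records of this trial, and those records contain no information about that error. If nothing is added, every replicate applies the same coefficients, and the spread on the plane reflects only the sampling variation of SDQ scores and costs. An error in a coefficient is common to all children, so recruiting more families does not reduce it. The plural in "using SDQ scores mapped onto a multi-attribute utility instrument using available algorithms" points to a second source that the bootstrap does not carry, the choice of algorithm.

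At stake is how far the child and dyad results can be trusted and compared with the parent result. The three acceptability curves would be drawn in the same way, but only the parent curve would be free of an omitted mapping component.

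**Working it through.** **The plan's own figures.** The article states no figure for mapping error or bootstrap width. The only usable inputs are in the Participants section: "To be able to detect an effect size of 0.35 with an alpha of 0.05 and power of 80" per cent, leading to 54 parents. The test is not stated. A one-sided paired t-test gives 52, a repeated-measures F-test over three occasions (f = 0.35/2 = 0.175, assumed correlation 0.5) gives exactly 54, and a two-sided paired t-test gives 67. So 54 can be reproduced under some readings. Allowing for 20% attrition, 54/0.80 = 67.5, or 68, which the plan rounds to 70.

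**Inputs for the illustration**
- n = 54. This is a count of parents. Only one parent per family may take part, so it is taken here as 54 children.
- d = 0.35, taken as the mean mapped change divided by its standard deviation. In the plan it is a detectable effect, not a forecast for the SDQ.
- c = relative standard error of the mapping slope. It is not in the documents; 5%, 10%, 20% and 30% are assumed.
- A linear mapping, so that the intercept cancels in a pre-post change and the QALY gain is proportional to slope times mean SDQ change.

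**Step 1: what the bootstrap sees.** The relative standard error of the mean change is s = 1/(d√n) = 1/(0.35 × √54) = 0.389.

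**Step 2: add the coefficient error.** For the product of two independent estimates, the combined relative standard error is √(s² + c² + s²c²). Divided by s, this is

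ratio = √(1 + c²(1 + nd²)), with nd² = 54 × 0.1225 = 6.615, so ratio = √(1 + 7.615c²).

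| c | combined relative SE | ratio to bootstrap SE |
|---|---|---|
| 5% | 0.392 | 1.01 |
| 10% | 0.403 | 1.04 |
| 20% | 0.444 | 1.14 |
| 30% | 0.505 | 1.30 |

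The ratio rises with n and with d, because the sampling part shrinks relative to the mean change while the coefficient part does not.

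**Step 3: the dyad.** The article does not define the dyad QALY. Assume that it is the sum of child and parent QALYs, with equal bootstrap standard errors and no correlation between them. Then ratio = √((2 + 7.615c²)/2) = 1.005, 1.02, 1.07 and 1.16 for the same four values of c. A positive correlation between child and parent would dilute the effect further.

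**Step 4: choice of algorithm.** No size can be given, because the article names no algorithm.

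**The case against.** The strongest reply is that this is a condensed journal article. A fuller health economic plan may exist, and drawing coefficients within replicates is the kind of detail it would hold. A reader might infer that the plan has decided to treat mapped utilities as if they were observed. The documents do not support that: the article neither says so nor excludes a comparison of algorithms. This part of the reply stands, and it is why the point is conditional. It does not remove the point, because the article does specify its uncertainty analysis, and the method it names cannot by itself carry error from outside the trial.

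A second reply is that the effect may be small, and this also stands. At coefficient errors of 5% to 10% it is 1% to 4%. Larger figures are tempting but unsupported:
- Doubling the standardised change to 0.70 gives ratios of 1.13, 1.45 and 1.86 at 10%, 20% and 30%, but 0.70 appears nowhere in the plan.
- Adding each child's mapping residual gives ratios of 1.29 to 3.21 for an assumed R² of 0.6 to 0.2. That compares mapped with directly measured utilities, which is a different question from coefficient error, and the documents give no R².
- With costs treated as known and a 30% coefficient error, the probability that the gain exceeds half its estimate falls from 0.90 to 0.85. That is not an acceptability-curve value. With cost uncertainty included (assumed relative standard error 30%) and a 10% coefficient error, the fall is only from 0.885 to 0.880.

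Nor is every probability pushed towards 0 or 1. Under this model the probability of any QALY gain is essentially unchanged even at 30% (0.995 against 0.9945).

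Finally, cost-effectiveness is a secondary objective resting on an uncontrolled pre-post contrast, and the Discussion concedes that the design cannot control for maturation or historical events. That limits the weight of this point but does not answer it.

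**Conclusion.** The point holds as a conditional one. The bootstrap as described leaves out error in the mapping coefficients and the choice of algorithm. Unless these are added, the child results understate uncertainty under both costing perspectives, and the dyad results do so to a lesser degree. The parent AQOL-8D analysis and the cost per improved case involve no mapping and are not affected.

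The direction is clear, but the size is not. The illustrative rise of 1% to 30% in the child standard error depends on the assumed coefficient error, on using 54 and 0.35 outside their original purpose, and on a linear mapping. At the lower end it would hardly change how the results are read; at the upper end it would be visible on the plane. This is an omission worth closing before the analysis, not a demonstrated error in a reported result.

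**What to change.** In the economic analysis plan, before results are seen:
1. Name one primary mapping algorithm and its target instrument.
2. Keep the planned bootstrap as the base case. Add a pre-specified sensitivity analysis for child and dyad QALYs in which each replicate first draws the mapping coefficients from their published covariance matrix, or from their standard errors if only those are available.
3. Repeat this under each other available algorithm.
4. Report the resulting planes and acceptability curves beside the base case, for both costing perspectives.

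A sensitivity analysis is preferable to a mandatory replacement of the base case, because a published covariance matrix may not be available. No new data are needed. The cost is slightly more analysis work and wider child and dyad intervals. Fixing the primary algorithm in advance also removes the possibility of choosing it after the results are known.

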### The group-based parenting intervention Everyday Life and Parenting

The Everyday Life and Parenting program targets parents of children aged 2–6 years with subclinical levels of NDDs and behavioral problems. These children are referred by child psychologists at the Uppsala Region’s child pediatric outpatient clinic. Families access the intervention through routine care triage, either from the waiting list or via recommendation by their consulting psychologist.

The Everyday Life and Parenting intervention consists of four modules. The intervention is theoretically based on social-learning theory [34] including ABA [35], the ICF framework and theory on emotion regulation [36, 37].

Three of the intervention modules include key components from the most effective parenting programs targeting behavior problems in children [24], including positive reinforcement techniques, relationship enhancement techniques and reframing unhelpful cognitive perceptions about the child, as well as emotion regulation knowledge and techniques. The fourth module is based on ABA and teaches a range of antecedent strategies [26, 35], such as how to organize the physical environment, how to use visual aids such as schemes of daily routines and time timers, and how to use high-probability request techniques. Furthermore, the modules include teaching parents general analytical and learning principles for teaching new skills or dealing with problem behaviors. In addition, parents are taught how to adapt activities and demands to the individual child, based both on his/her strengths, and on cognitive and adaptive abilities. Parents also practice reflecting on their own emotions, cognitions and abilities in order to find ways of adjusting and adapting to improve their own and their child’s well-being. This holistic approach to the child’s and the parents’ functioning is in line with the ICF framework. The delivery format of the intervention is also based on well researched components [38] and includes providing psychoeducation; discussions; formulating goals and goal attainment; homework assignments and peer support. Each module lasts 3 h and the intervention is given every other week for 8 weeks.

Depending on the parents’ preferences, the intervention is delivered either entirely on-site or digitally. In the digital option, the first session is on-site to allow parents to get to know each other. The other sessions are digital.

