Groups of Everyday Life and Parenting start four to six times every term. Each group includes parents from up to 10 families, i.e., in total 20 parents. Both parents are encouraged to participate in the intervention.

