**Resource use.** Costs related to the consumption of societal resources will be collected using an adapted version of the Trimbos/iMTA questionnaire for costs associated with Psychiatric Illness (TIC-P). It comprises information on the use of resources related to healthcare, medication and supplements, social support and assistance, and productivity losses due to absence from paid and unpaid work for parents for care of a sick child [47].

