#### Child medical records

The following health data will be collected: number of healthcare visits (e.g. doctor, nurse, speech therapist, psychologist, dietician, physiotherapist), visits to the emergency department, inpatient care, prescribed drugs, referrals, child development with regard to symptoms of NDDs.

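### The health care provider perspective counts programme cost only, so its ICER cannot reflect any change in use of the provider's own services

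*Protocol article*

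**What the plan says.** The Health economic evaluation section of the protocol article sets two cost perspectives. On the first it says "The health care provider perspective includes the cost to run the intervention (e.g., therapist salary costs, administration", with these costs taken from project documentation at the clinic. On the second it says "The societal perspective includes, in addition to intervention costs, other health care costs (health care utilization and medication", followed by costs beyond health care, among them "indirect costs related to lost productivity for parents (related to absence from paid and unpaid work) collected via the TIC-P". ICERs are then formed from pre-to-post differences in cost and in effect, separately for each perspective.

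Health-care use is measured twice. The Child medical records section lists the child's health-care visits as well as "visits to the emergency department, inpatient care, prescribed drugs, referrals", and the Procedure section says these data come from the Region's electronic record system. The Resource use paragraph adds an "adapted version of the Trimbos/iMTA questionnaire for costs associated with Psychiatric Illness (TIC-P"), which also covers health care and medication. That paragraph describes the questionnaire's productivity item as "productivity losses due to absence from paid and unpaid work for parents for care of a sick child".

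On the time the programme asks of parents, the intervention section describes four modules and states: "Each module lasts 3 h and the intervention is given every other week for 8 weeks". It adds: "Both parents are encouraged to participate in the intervention".

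**The concern.** A provider deciding whether to run the programme wants its net cost: what the programme costs, plus or minus any change in visits, admissions and drugs. The stated boundary keeps the second part out of the perspective that carries the provider's name. The families are patients of the Region's own outpatient clinic, and the relevant data are drawn from the Region's own records. The omission is therefore not forced by lack of data.

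The consequence is an ICER, a cost-effectiveness plane and an acceptability curve labelled as the provider's view that would look the same whether service use fell, rose or stayed level after the programme.

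A smaller question concerns the societal perspective. Its productivity loss comes from the TIC-P. If that questionnaire asks only about caring for a sick child, the hours parents spend in sessions would not be recorded by it.

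**Working it through.** **Provider perspective**

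Let P be programme cost per family, U the cost of other health-care use per family over a comparable window, and ΔE the pre-to-post change in effect (improved cases or QALYs).

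1. Boundary as stated: cost before = 0, because the programme has not yet been delivered; cost after = P. The increment is P − 0 = P, and the ICER is P / ΔE.
2. Boundary with health-care use: cost before = U_pre; cost after = P + U_post. The increment is P + (U_post − U_pre), and the ICER is [P + (U_post − U_pre)] / ΔE.
3. The two ICERs differ by (U_post − U_pre) / ΔE. If use fell by exactly P, the second ICER would be 0 while the first stayed at P / ΔE.

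The documents give no value for P or U, so the difference cannot be put in money. Its form is nevertheless certain: the whole change in service cost is excluded.

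There is also an effect on the uncertainty analysis. If P is entered as an average per family (an assumption; the article does not say), resampling families adds almost no variation in provider cost. The provider plane and curve would then show little beyond uncertainty in the effect.

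**Scope of productivity loss**

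| Place in the article | Scope described |
|---|---|
| Resource use paragraph | Parents' absence to look after a sick child |
| Health economic evaluation | Parents' absence from paid and unpaid work, no reason specified |

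Both describe data from the same questionnaire, and the first is narrower than the second.

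**Parents' session time**

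The article states no total, so there is no figure to reproduce.

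- Per parent attending every module: 4 modules × 3 h = 12 h.
- Per family if both parents attend every module: 2 × 12 h = 24 h. This is an upper bound, because joint attendance is encouraged and not required.
- Per full group of 10 families: 10 × 12 = 120 parent-hours with one parent each, and 20 × 12 = 240 with two.

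Travel and homework are excluded.

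**The case against.** The case for the plan has four parts.

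- The provider boundary is openly stated and fits the budget view of the clinic that delivers the programme.
- Health-care use is not lost from the evaluation, because it enters the societal analysis, where savings or added use can appear.
- The comparison is uncontrolled. The Discussion accepts that time-related confounding cannot be excluded, and families enter by referral or from a waiting list. A before-after change in visits may therefore reflect the care pathway and not the programme.
- Cost-effectiveness is a secondary objective, and the primary outcomes are untouched.

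All of this stands, but it does not rescue the label. The verb used for the provider perspective might be read as open-ended, yet the next sentence assigns the missing items elsewhere. A programme-budget figure is legitimate if it is called that. Confounding by time is a reason for caution in interpretation, but it applies equally to the effects in the denominator.

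A reader might go further and infer that the societal perspective omits parents' session time altogether. The documents do not support that. The Health economic evaluation section does not limit the reason for absence, its list of costs beyond health care is open, the TIC-P is an adapted version whose items are not shown, and no section excludes session time. A condensed article may also leave itemised costing to a fuller document.

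A reader might also infer that parents' time outweighs staff time or dominates programme cost. That cannot be shown either. The number of leaders is not stated, ten families is a maximum group size, and hours are not costs.

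**Conclusion.** The provider half is firm and rests on the article's own definitions. As planned, the provider increment equals programme cost, and the provider ICER leaves out the entire change in the provider's service use. The size in money is unknown because the documents give no costs. The only assumption is that no programme cost arises before the programme is delivered.

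The societal half holds only as an inconsistency: two descriptions of the same questionnaire differ in scope, and the article does not settle whether session time is costed. The quantity in question is 12 h per parent with full attendance, and at most 24 h per family.

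Both matters concern a secondary objective. They should be settled before the cost data are analysed, so that the boundaries are not chosen after the results are known.

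**What to change.** 1. **Provider perspective.** Add the child's health-care visits, emergency visits, inpatient care and prescribed drugs to programme cost. Name one source per item: medical records for the child's use, and the TIC-P only for items the records do not hold. Without that rule the same visit or drug could be counted twice. If the narrower boundary is preferred, keep it and call the result a programme-cost ratio.
2. **Productivity loss.** Reconcile the Resource use paragraph with the Health economic evaluation section and state what the adapted TIC-P asks.
3. **Session time.** If the TIC-P does not capture it, add modules attended × 3 h × number of parents attending to the societal perspective, valued as other paid and unpaid work is valued.

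The first change reassigns data already planned for collection. Its price is that provider costs become more variable and that the before-after change in use remains uncontrolled, which the report should say.

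The third change may need new data. The fidelity checklist records which session elements were completed, the background questions ask only whether someone else in the family takes part, and no attendance record is described. Data collection began in August 2024, so attendance at finished groups may have to be obtained from the clinic. Where it cannot be, a sensitivity analysis with 12 h and 24 h per family would show the result under full attendance by one or two parents.

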### Materials

Primary outcomes are assessed through the parent SCED data collection, while the secondary outcomes are assessed through child SCEDs, pre/post-measures and the child’s medical records.

Primary outcomes.

Child behavior problems.Parental self-efficacy.Parental stress.

Secondary outcomes.

Child mental health problems.Parents’ mental health.Parents’ quality of life.Goal attainment and client satisfaction.Child medical data.Children’s positive and negative experiences of family life.

In the current study, data are collected from five sources:

Parent weekly short measures.Validated questionnaires at pre-, post- and 3-month follow-up (T1, T2, T3).Forms on goal, goal attainment and client satisfaction with the intervention.Data from the child’s medical records.Child weekly short measures.

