### Procedure

Parent weekly measures will be collected via telephone by research assistants, with responses entered into REDCap. Data collection spans 15, 18, or 21 weeks, depending on the participant’s baseline length (4, 7, or 10 weeks). Pre-, post-, and 3-month follow-up questionnaires will also be distributed via REDCap, with pre-measures sent before baseline and post-measures after the intervention. Goal setting, goal attainment, and client satisfaction forms will be sourced from the Everyday Life and Parenting materials.

Child health data will be obtained through the Uppsala Region’s procedure for accessing research data from the electronic medical record system Cosmic. Child weekly measures will be sent digitally via REDCap and completed during the same weeks as the parent measures.

Intervention fidelity will be assessed through a checklist completed by course leaders after each module, indicating which session elements were completed.

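### Area under the curve is prescribed for costs as well as QALYs; applied to TIC-P costs, it would put pre-baseline resource use into the trial total and let the T3 report fill only half of follow-up

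*Protocol article*

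**What the plan says.** The Health economic evaluation section gives one rule for two quantities: "Total costs and total QALYs will be aggregated over the trial period and estimated using the area under the curve method". The next sentence has regression models analyse differences in total costs, QALYs and improved cases before and after the intervention. The ICER is then defined from pre-post differences. There is no control arm.

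The cost data have three possible sources:

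- Intervention cost, which is what the health care provider perspective is said to include, comes from project documentation at the clinic.
- For the wider societal costs, the Resource use paragraph says: "Costs related to the consumption of societal resources will be collected using an adapted version of the Trimbos/iMTA questionnaire". This questionnaire is listed among the pre-, post- and 3-month follow-up measures (T1, T2, T3). No recall window is stated.
- The Child medical records section collects "number of healthcare visits (e.g. doctor, nurse, speech therapist, psychologist, dietician, physiotherapist), visits to the emergency department, inpatient care, prescribed drugs". The costing paragraphs do not say whether these records are used.

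On timing, the Procedure section has questionnaires sent "with pre-measures sent before baseline and post-measures after the intervention". So T1 precedes the baseline phase.

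**The concern.** Utility is a level: a value at T1 and a value at T2 can be joined by a line, and the area beneath it is a sensible QALY estimate. A resource-use report is already a total over a past period. Laying a trapezoid through three such reports treats each as an instantaneous rate at the date of completion. Two things follow. The T1 report can only describe use before baseline, yet it becomes part of the trial-period total. The T3 report, which looks back over follow-up, is credited with half of that interval, and the T2 rate fills the other half.

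The rule also conflicts with the before-after comparison in the same section. In a single-arm study the pre-intervention cost is the comparator. If the T1 report also sits inside the total, the same data stand on both sides of the contrast.

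At stake is the cost side of the societal ICERs, and with it the bootstrap plane and acceptability curve for that perspective.

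**Working it through.** The article states no cost figure, so there is nothing to reproduce. The check compares the weights implied by the stated rule with those of direct summation.

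**Inputs from the article**
- Intervention length: "Each module lasts 3 h and the intervention is given every other week for 8 weeks".
- Baseline length: 4, 7 or 10 weeks, with weekly data collection of 15, 18 or 21 weeks (Procedure). These lengths are described for the participants giving weekly measures.
- Follow-up: 3 months after T2.

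**Assumptions**
- The area is a trapezoid.
- T2 falls at the end of the 8-week intervention, and 3 months is 13 weeks.
- For the comparison with summation, each recall window covers the whole preceding interval.

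**Formulas.** Let t12 be the weeks from T1 to T2, t23 = 13 the weeks from T2 to T3, and c1, c2, c3 the weekly cost rates reported at T1, T2, T3.

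- Trapezoid: (t12/2)·c1 + ((t12 + t23)/2)·c2 + (t23/2)·c3
- Direct sum: t12·c2 + t23·c3
- Trapezoid minus sum: (t12/2)·(c1 − c2) + (t23/2)·(c2 − c3)

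**Weights in weeks**

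| Baseline | t12 | T1 / T2 / T3 weight | Total | T1 share |
|---|---|---|---|---|
| none | 8 | 4 / 10.5 / 6.5 | 21 | 19% |
| 4 weeks | 12 | 6 / 12.5 / 6.5 | 25 | 24% |
| 7 weeks | 15 | 7.5 / 14 / 6.5 | 28 | 27% |
| 10 weeks | 18 | 9 / 15.5 / 6.5 | 31 | 29% |

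Under direct summation the T1 weight is 0 and the T3 weight is 13. If T2 instead falls when weekly collection ends (15 − 4 = 11 weeks after the baseline phase), the T1 shares for the three staggered baselines become 7.5/28 = 27%, 9/31 = 29% and 10.5/34 = 31%.

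**Size in money.** The weekly rates below are illustrative; t12 = 12.
- Constant, 100/100/100: sum 2500, trapezoid 2500, error 0.
- Falling, 200/100/50: sum 12·100 + 13·50 = 1850; trapezoid 6·200 + 12.5·100 + 6.5·50 = 2775; error +925, or +50%.
- Rising at the end, 100/100/150: sum 3150, trapezoid 2825, error −325, or −10%.

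**Recall window.** The trapezoid multiplies each unit of cost reported at T3 by 6.5 divided by the window; full scaling to the interval multiplies it by 13 divided by the window.
- 13 weeks: 0.50 against 1.00.
- 8 weeks: 0.81 against 1.625.
- 4 weeks: 1.625 against 3.25.

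The trapezoid always gives half of full scaling. It gives half of the actual cost only when the window equals the interval.

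**The case against.** The strongest reply is that the sentence is compressed: costs may be meant to be aggregated and only QALYs estimated by area under the curve, with the detail left to the cited method and a fuller plan. That may be the intention, but the sentence joins both quantities to one method. This is a rule stated for data it does not fit, not an omitted detail. It does stand that the trapezoidal form and the recall window are assumed here.

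Other limits also stand. The staggered baselines belong to the single-case part (about 18 parents to be recruited), while the pre-post-follow-up sample is 70 recruited, so 19% may apply to most of the sample. These are time weights, not bias; the article gives no cost data or trend from which bias could be computed. With a short recall window a report is closer to a rate, interpolation is less clearly wrong, and full scaling inflates a single event more than the trapezoid does (3.25 against 1.625 at 4 weeks).

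A reader might infer more than the article supports:
- That every ICER is affected. The provider perspective rests on clinic documentation and is untouched.
- That a cost incurred in follow-up always counts half. That needs a 13-week window.
- That pre-study cost necessarily dilutes any change in resource use. The two terms of the error can differ in sign, and the article does not say how the total enters the before-after difference.
- That the medical records are ignored. The mention of the TIC-P closes a long list and does not clearly exclude them.

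**Conclusion.** The point holds for the TIC-P part of the societal perspective. Followed as written, the rule gives pre-baseline resource use about 19% of the time weight with no staggered baseline and 24% to 29% with one, and lets the T3 report fill half of the T2–T3 interval. This assumes a trapezoid, T2 at the end of the intervention and a 13-week follow-up.

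The monetary error is zero under constant cost rates. If costs fall steadily the total is too high, and if they rise it is too low. The defect is clearest when the recall window covers the whole interval. The conflict with the before-after comparison does not depend on the window: T1 cost cannot be both the comparator and part of the total compared with it.

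Cost-effectiveness is a secondary objective, and the effectiveness analyses are unaffected. The wording should be corrected before the economic analysis.

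**What to change.** Amend the Health economic evaluation section as follows:

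1. Restrict area under the curve to QALYs.
2. Define total cost after T1 as the sum over non-overlapping periods (T1–T2 and T2–T3), with intervention cost added from clinic documentation.
3. State the TIC-P recall window. Scale T2 and T3 TIC-P costs to the interval by a stated rule, and only where the window is shorter than the interval.
4. Keep the T1 TIC-P cost, standardised to the same length of time, as the pre-intervention comparator and outside the post-T1 total. Using it only as a covariate would leave this single-arm design without the pre-intervention cost that its ICER needs.
5. Where the dated medical-record data already being collected cover the child's care, sum that care directly from them, and say which items come from records and which from the TIC-P so that none is counted twice.

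The cost is a change of wording and a little more analysis and linkage work; no new data are needed. Scaling from a short recall window remains an approximation.
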